### Intervention

2.6

A total of 30 patients will receive daily oral doses of 3000 mg of a commercially available multistrain probiotics produced by Allergosan, Graz, Austria (‘OMNI‐BIOTIC Stress Repair’ including the following bacterial strains: *Lactobacillus casei* W56, *Lactobacillus acidophilus* W22, *Lactobacillus paracasei* W20, *Bifido‐bacterium lactis* W51, *Lactobacillus salivarius* W24, *Lactococcus lactis* W19, *Bifidobacterium lactis* W52, *Lactobacillus plantarum* W62 and *Bifidobacterium bifidum* W23) for a duration of 6 months (once daily). The probiotics used in this study are a commercially available dietary supplement. No side effects are known. The participants are informed that they may experience minor gastrointestinal inconvenience at the beginning (e.g., minor abdominal fullness, flatulence, minor constipating or laxative effects). 30 patients will receive placebo (also prepared by Allergosan). The ingredients of the placebo are made up of maize starch, maltodextrin, potassium chloride, magnesium sulphate and manganese sulphate. The study medication (probiotics and placebo) is a vegan product. The administration of placebo is necessary for the successful blinding of participants and the research staff.

The participants will be trained for the self‐administration of probiotics/placebo by the nursing staff, who observes the continuous administration for the time of the inpatient stay. After discharge, the patients and the parents/caregivers get a written instruction for the further administration, which is attached to the ‘medication’ box. The participants are asked to collect the daily sachets—empty or full—in the box to comprehend the number of taken and not taken probiotics. For further questions, especially for the intervention of the probiotic administration, the contact of the research team is provided in the patient letter.

### Randomisation

2.7

Randomisation will be carried out double‐blind by the Institute of Medical Informatics and Statistics, University of Kiel (Germany). Each patient will be allocated to one of the two treatment conditions (probiotics or placebo) in a 1:1 ratio. Randomisation will be stratified for the clinical centre (Vienna and Innsbruck study site) and atypical/typical AN according to International Classification of Diseases and Related Health Problems—10th revision (ICD‐10; World Health Organization, 2009) (i.e. whether the age‐ and sex‐specific BMI percentile at admission is above or below 10). Experimental conditions will be randomized in blocks of four individuals for patients with typical AN and in blocks of two for atypical AN participants. Block randomisation is performed using the R package randomiseR (Uschner et al., 2018).

In order to ensure a proper randomisation procedure, the study medication (probiotics or placebo) is prepared for each individual participant by the same company (Allergosan) and consecutively numbered. The number does not allow any conclusion about the group (probiotic vs. placebo). The allocation list is exclusively sent to the Institute of Medical Informatics and Statistics, University of Kiel (Germany) which performs the randomisation and informs the clinical centre about the number of the study medication that should be given to the individual participant. All other parties involved, including patients, clinicians and research staff who are responsible for recruiting participants and obtaining data for the evaluation of this study have no insight into the allocation list until the blinding is removed at the end of the study (after the final patients has completed the 12‐month follow‐up assessment). Importantly, probiotics and placebo do not differ regarding packaging, smell, taste and appearance.

### Measures and instruments

2.8

In order to evaluate the effect of probiotic administration in patients with AN, various measures are obtained at baseline, discharge, post‐intervention and 12‐month follow‐up. Assessments at discharge are omitted if the post‐intervention assessment (6 months after baseline) is scheduled 2 weeks before or one month after discharge. A complete list of all measures and instruments used in patients and healthy controls including the time points when they are assessed is provided in Table 1.

**TABLE 1 erv2876-tbl-0001:** Summary of measures and instruments used in the present study

Instrument/measure	Domain/aim	Time point^a^			
		T_A_	T_D_	T_6_	T_12_
Sociodemographic questionnaire	Key sociodemographic and clinical data	x	–	–	–
Body‐mass‐index (BMI)	Weight/weight gain	x	x	x	x
Eating disorder examination interview (EDE; Cooper & Fairburn, 1987)^b^	Eating disorder diagnosis and symptomatology	x	x	x	x
Eating disorder examination questionnaire (EDE‐Q; Hilbert et al., 2007)	Eating disorder symptomatology (self‐report)	x	x	x	x
Eating disorder inventory‐2 (EDI‐2; Garner, 1991)	Eating disorder symptomatology	x	x	x	x
MINI interview/MINI‐KID interview (Sheehan et al., 1998)	Psychiatric comorbidity	x			
Beck depression inventory‐II short version (Beck et al., 2006)	Level of depression	x	x	x	x
State‐trait anxiety inventory (state part only) (Spielberger, 2010)	Level of anxiety	x	x	x	x
Yale‐brown obsessive compulsive scale (Y‐BOCS; Goodman et al., 1989)	Obsessive compulsive thoughts and behaviours (self‐report and expert rating)	x	x	x	x
Social responsiveness scale (SRS) (Bölte & Poustka, 2007)^b^	Autistic traits (parent report)	x	‐	x	x
Gastrointestinal complaints questionnaire (Cuntz & Hiller, 1998)	Gastrointestinal complaints	x	x	x	x
Iowa gambling task (IGT; Bechara et al., 1994)	Executive functioning (decision‐making processes)	x	‐	x	x
Probabilistic reversal learning task (PRLT; Cools et al., 2009)	Cognitive flexibility	x	‐	x	x
Food and non‐food related Go/No go task (Rosval et al., 2006)	Sustained attention and response control	x	‐	x	x
UPPS‐P impulsive behaviour scale (negative urgency‐scale only) (Whiteside & Lynam, 2001)	Level of emotion‐driven impulsiveness	x	‐	x	x
BIS/BAS questionnaire (Carver & White, 1994)	Sensitivity for reward and punishment	x	‐	x	x
Wechsler intelligence test (two subtests: Matrices and vocabulary) WISC‐V (Petermann, 2017) or WAIS‐IV (Petermann, 2012)	Intelligence	‐	‐	x	‐
Stool sample	Composition of the gut‐microbiome	x	x	x	x
Food protocol	Dietary intake during 48 h prior stool sampling	x	x	x	x
Actimetre/physical activity tracker	Amount of physical activity (steps, active hours) during 48 h prior stool sampling	x	x	x	x
Serum/plasma sample	Diverse blood parameters including Hormones, gut permeability parameters (serum zonulin), systemic inflammation markers (interleukin IL‐6), hunger and satiety markers (ghrelin, α‐MSH‐reactive IgG)	x	x	x	x
(Functional) magnet resonance imaging^c^	Analysis of the underlying mechanism of the gut‐brain interaction	x	‐	x	x

^a^
Definition of assessment time points: T_A_ baseline assessment at admission, T_D_ discharge assessment (only in anorexia nervosa patients), T_6_ post‐intervention assessment (6 months after baseline), T_12_ 12‐month follow‐up assessment.

^b^
Assessed in anorexia nervosa patients only (not in healthy controls).

^c^
Assessed in 30 anorexia nervosa patients and 60 healthy controls only.

#### Primary outcome measure

2.8.1

The primary outcome measure is defined as the body‐mass‐index (BMI) and sex‐ and age‐specific BMI percentiles based on KIGGS reference data (Robert Koch Institute, 2013). Height and weight measures are taken by trained nurses.

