#### Primary hypothesis

2.1.1

Patients with AN who receive a probiotic supplementation for 6 months show greater weight gain compared to patients who receive placebo.

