### Sample size considerations

2.12

So far, no studies on the specific effects of a probiotic intervention in patients with AN are available. A small study that investigated the effects of providing omega‐3 poly‐unsaturated fatty acids (PUFA) compared to saturated fatty acids in patients with AN found an effect in weight gain of *d* = 1.0 (Mauler et al., 2009). Meta‐analyses of probiotic interventions in depression and anxiety disorders revealed a pooled effect of *d* = 0.68 for improvements in depressive symptoms and *d* = 0.66 for improvements in anxiety symptoms compared to placebo (Huang et al., 2017). Thus, for the present study we assumed an effect size of *d* = 0.75 for the effect of probiotics compared to placebo on the change in BMI. To detect this effect using a two‐sided *t*‐test with a power of 80% at a significance level of 0.1, a sample size of 24 patients per group is needed. Considering a dropout rate until the 12‐month follow‐up of about 10%, 30 patients per group, respectively, 60 patients in total will be included in the trial. The final analysis will be performed after the complete follow‐up of all the patients. In case the final analysis will include 30 patients per group, the expected power (assuming an effect size of *d* = 0.75) will be 88%. For effect sizes of *d* = 1.0 and *d* = 0.65 as reported by previous studies mentioned above, the achieved power will be 98% and 80%, respectively.

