### Statistical analysis plan

2.13

The primary analysis will be based on the intention‐to‐treat principle (ITT), including all randomized patients irrespective of the amount of treatment actually received. A per‐protocol analysis will be performed as sensitivity analysis. In order to follow ITT principle as closely as possible, all participants will be asked to participate in the end‐of‐treatment and follow‐up assessment (at 6 months and 1 year), in particular regarding BMI measurement, even if they drop out of treatment, to minimise the amount of missing data.

We will test for a difference in the primary outcome measure (age‐adjusted BMI at 1 year follow‐up) between the probiotics and placebo arm using a mixed‐effects model repeated measures analysis with covariates study site, sex, atypical/typical AN, and BMI at admission and will include any available further measurements of BMI (in particular at discharge and month 6). As this is equivalent to a phase II trial, emphasis will be on the 95% confidence intervals of the effect size estimates; additionally, *p*‐values will be calculated.

Secondary outcomes such as eating disorder pathology and changes in the gut MI will be analysed in a similar way, additionally using measures of MI community composition and diversity measures, mostly in a descriptive way.

In addition to the randomized comparison between probiotics and placebo groups, a comparison between healthy controls and patients (in both arms) will be done to assess both differences in gut MI composition and diversity between patients with AN and healthy controls in the most acute phase of disease (at admission to inpatient treatment) and to assess the size of changes during and after treatment and weight rehabilitation in patients with AN compared to natural fluctuations of MI composition in healthy adolescents during normal development. Again, mixed‐effects models repeated measures analyses with an emphasis on descriptive reporting of confidence intervals of effect sizes will be performed.

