In this clinical trial, any missing values of the primary outcome variable have to be considered to be missing not at random (MNAR). In particular patients with very poor response to the intervention and the standard multi‐modal treatment of AN that is the same in both arms, might be more likely to drop out of treatment and might be more likely not to provide data on the primary outcome (loss to follow‐up). Thus, imputation strategies or analysis methods that rely on the missing at random (MAR) assumption could be anti‐conservative. However, every effort will be made to keep missing data as low as possible. In the primary analysis of the primary endpoint, we will use all available measures of the primary outcome BMI at all time points in a mixed‐effects model repeated measures analysis.

Sensitivity analyses will be performed to investigate the potential impact of missing data, in particular, by performing a complete case analysis, a pre‐specified conservative single imputation approach and by using multiple imputations.

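### The primary outcome is named on different scales (BMI, BMI percentile, change in BMI, an undefined age-adjusted BMI), and nothing says which one the primary test uses

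*Protocol article*

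**What the plan says.** Five statements in the protocol article bear on the primary outcome.

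- Section 2.1.1 (Primary hypothesis) expects that patients given probiotics "for 6 months show greater weight gain compared to patients who receive placebo".
- Section 2.8.1 (Primary outcome measure) defines the outcome as "BMI) and sex‐ and age‐specific BMI percentiles based on KIGGS reference data". No time point is given there.
- Section 2.12 (Sample size considerations) assumes d = 0.75 "for the effect of probiotics compared to placebo on the change in BMI".
- Section 2.13 (Statistical analysis plan) tests the "primary outcome measure (age‐adjusted BMI at 1 year follow‐up") in a repeated-measures mixed model "with covariates study site, sex, atypical/typical AN, and BMI at admission".
- The missing-data paragraphs of section 2.13 say of the same analysis: "we will use all available measures of the primary outcome BMI at all time points".

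No BMI-SDS, z-score or percent of median BMI appears anywhere. The KIGGS percentile is the only age-adjusted form of BMI that the article names.

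**The concern.** A primary test needs one variable. The two scales in section 2.8.1 are joined without a rule for choosing, and the later sections do not settle it. Raw BMI fits sections 2.12 and the missing-data text but not the age-adjusted outcome of section 2.13. An age-adjusted scale fits section 2.13 but not the other two. The model has no age term, so any age adjustment must sit in the outcome itself, while the baseline covariate is not described as age-adjusted.

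This matters because the patients are 13 to 19 years old and are followed for a year, so the same BMI stands for a different position relative to peers at different ages. The choice of scale can change the result. If it is still open when the blind is broken, it cannot be shown to be independent of the data. The one age-adjusted form that is named, the percentile, also gives little weight to gains made at very low BMI.

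**Working it through.** **1. The plan's own figures.** Inputs from section 2.12: d = 0.75, two-sided alpha 0.10, 80% power. A two-sample t-test (noncentral t) needs n = 22.7, so 23 per group, against 24 stated. With 30 per group, power is 89.0%, 98.6% and 80.0% for d = 0.75, 1.0 and 0.65, against 88%, 98% and 80% stated. The figures reproduce closely. The defect is in what d refers to, not in the arithmetic.

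**2. How many different variables are there?** With the baseline on the same scale as covariate, change and follow-up value give the same test. If Y12 - Y0 = a + b·arm + c·Y0, then Y12 = a + b·arm + (c + 1)·Y0, and the treatment effect b is unchanged. Change against value is therefore not the problem. What remains is raw against age-adjusted BMI and, within age-adjusted, percentile against some other score.

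**3. Percentile compression.** Assume a normal reference, percentile = 100·Φ(SDS).
- From SDS -3 to -2: 0.13 to 2.28, a gain of 2.1 points.
- From SDS -1 to 0: 15.87 to 50.00, a gain of 34.1 points.

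The same 1-SDS gain counts 34.1 / 2.1 = about 16 times as much in the second case.

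**4. What the choice of scale would cost if the percentile were tested.** Per group, 30 × (1 - 0.10) = 27 patients, using the 10% dropout of section 2.12. SDS is drawn as Normal(m, 1) on placebo and Normal(m + 0.75, 1) on probiotics, with 20,000 trials per setting and a t-test at 0.10 on each scale. The 12-month placebo mean m is an assumption, because the article gives none.

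| Assumed placebo mean SDS at 12 months | Power on SDS | Power on percentile | The two tests disagree |
|---|---|---|---|
| -2.0 | about 86% | about 76% | about 14% |
| -1.5 | about 86% | about 81% | about 9% |
| -1.0 | about 86% | about 83% | about 6% |
| -0.5 | about 86% | about 84% | about 4% |

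With no treatment effect, the percentile t-test kept close to its nominal 10% in every setting. The cost is power, not validity.

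**5. What it would cost if success on either scale counted.** For two test statistics with correlation r, each tested at |z| > 1.645, the chance of at least one false positive is 12.6% (r = 0.95), 13.6% (r = 0.9), 15.0% (r = 0.8) and 16.1% (r = 0.7). The correlation is assumed. The null simulation of step 4 gives about 0.81 at m = -2 and 0.97 at m = -0.5, so the lower part of this range is the more likely one.

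**The case against.** The strongest reply is that this is loose wording in a condensed article and that the full protocol or analysis plan will define the transformation. The age-adjusted BMI of section 2.13 could well mean a BMI-SDS, and BMI at admission could be shorthand, since the same sentence also writes plain BMI for the repeated outcome measurements. That is a fair reading. It does not remove the point, because the article does more than leave a detail out: its own sections name different scales for one test.

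Several stronger readings are tempting, and the text does not support them.

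- *There are four different primary measures.* A reader might count four, but the age-adjusted BMI may simply be the percentile at 12 months, and change and adjusted follow-up value are the same test on one scale.
- *The time point is open.* Section 2.13 fixes it at 1 year. The 6 months in the hypothesis describe how long the supplement is taken.
- *The plan fits a normal-theory model to percentiles.* No section says that the percentile enters the model.
- *The error rate is above nominal.* No section declares success on either measure. Section 2.13 names one test, likens the trial to phase II and puts the emphasis on confidence intervals.
- *All of these patients sit at the floor of the percentile scale.* Atypical AN is eligible and is stratified as above the 10th percentile. The endpoint also comes 12 months after baseline, following treatment that aims at a healthy weight.

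**Conclusion.** The point holds as an inconsistency in the definition of the primary outcome. The article does not say on which scale its single primary test is run, nor on which scale d = 0.75 is assumed, and its sections cannot all be followed at once.

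The numerical consequences are conditional. If the percentile were used, power would be lower by about 10 points at an assumed placebo mean SDS of -2 and by 1 to 2 points at -0.5, and at -1.5 or above it would still meet the planned 80%. These figures rest on a normal reference, SD 1, 27 per group and an unadjusted t-test, as in the plan's sample size calculation, and not on the mixed model. If either scale could count as success, the false-positive rate would be about 13% to 16%, but no such rule is stated. The case for correction rests on the contradiction and on the 4% to 14% of trials in which the choice of scale would decide significance.

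**What to change.** Before unblinding, name one primary variable: BMI-SDS from the KIGGS reference at the 12-month assessment, which is the time point section 2.13 already uses. Make baseline BMI-SDS the covariate in place of BMI at admission. State in section 2.12 that d = 0.75 refers to this variable. List raw BMI and BMI percentile as supportive. Reword sections 2.1.1, 2.8.1, 2.12 and both parts of 2.13 so that they all name it.

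The cost is wording and one transformation. Height, weight, age and sex are already needed for the percentile, so no new data are required. If d = 0.75 is accepted on the SDS scale, the sample size stands. The one drawback is that SDS is less intuitive to clinical readers, so the difference in kg/m² should be reported alongside.

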#### Secondary outcome measures

2.8.2

The comprehensive test battery for the secondary outcome include in‐depth assessment of the eating disorder diagnosis and symptomatology using a gold‐standard clinical interview (Cooper & Fairburn, 1987) and self‐report instruments (Garner, 1991; Hilbert et al., 2007), and assessment of comorbid psychiatric disorders using a structured diagnostic interview (Sheehan et al., 1998) and self‐report questionnaires for depression (Beck et al., 2006), anxiety (Spielberger, 2010), obsessive compulsive thoughts and behaviours (Goodman et al., 1989) and autistic traits (Bölte & Poustka, 2007). Gastrointestinal complaints are obtained by obtaining the frequency of and distress caused by 17 gastrointestinal symptoms (e.g. flatulence, stomach ache, very hard or soft defecation, regurgitation) (Cuntz & Hiller, 1998). Moreover, a battery of neuropsychological tests are obtained including measures of decision making processes (Bechara et al., 1994), cognitive flexibility (Cools et al., 2009), sustained attention and response control (Rosval et al., 2006), level of emotion‐driven impulsiveness (Carver & White, 1994), sensitivity for reward and punishment (Carver & White, 1994) and a brief assessment of intelligence (Petermann, 2012, 2017).

Furthermore, stool samples are collected at each time point to analyse the composition of the gut MI. We also obtain the dietary intake by food protocols and the level of physical activity by using an actimeter/fitness tracker (Fitbit, Inc.) during 48 h prior to the collection of stool samples as it is known that the gut MI is influenced by the composition of the nutrients that are ingested and the amount of physical activity. We also collect information about alcohol (Engen et al., 2015) and drug consumption (Meckel et al., 2019), medication use (Bahr et al., 2015; Maier et al., 2018) including antibiotics (Arnau et al., 2020) and prebiotics (Parnell et al., 2012) during the previous six months as these factors are known to impact the gut MI. Moreover, previous infection with COVID‐19 and COVID‐19 vaccination status is obtained as their influence on the intestinal MI is still unknown; however, first evidence indicate that the MI may moderate the effectiveness of the vaccination (Lynn et al., 2021).

We also take serum/plasma samples to analyse markers of gut permeability (serum zonulin), systemic inflammation (interleukin IL‐6), hunger and satiety (ghrelin, α‐MSH‐reactive IgG) as well as hormones (e.g., LH, FSH, cortisol).

Finally, we also conduct structural (sMRI) and functional magnet resonance imaging (fMRI) to better analyse the underlying mechanism of the gut‐brain‐interaction in a subsample of patients with AN and healthy controls. Details regarding the sMRI and fMRI procedure will be published in a separate protocol paper.

### Storing and processing of blood and stool samples

2.9

Blood serum samples will undergo centrifugation and are separated into aliquots of 500 µl and stored at −80°C. Analysis for inflammatory markers, gut permeability markers and hormones will be conducted using ELISAs.

For the collection of stool samples the patient is instructed to line the toilet bowl with toilet paper before defecation to guarantee an accurate sample collection. Further, they are instructed to put three pea‐sized amounts of stool with the spoon, which is attached to the stool tube, into the tube and then to cap the tube.

After collection, the stool samples will be sent to the Biobank, divided into three aliquots and frozen at −80°C as fast as possible (usually within 24 h). For follow‐up assessments and healthy control subjects, stool tubes are sent by post or provided at an appointment at the clinic. They are instructed to collect the stool sample at home and bring it to their appointment at the clinic. The stool sample is then stored within 48 h.

In order to analyse the MI composition frozen stool samples collected from patients and HC will be subject to microbial genomic DNA extraction. Briefly, total DNA will be extracted using the QIAamp PowerFecal DNA Kit (Qiagen), following the manufacturer's protocol. The V3‐V4 region of the 16S rRNA gene will be amplified and sequenced on an MiSeq Illumina sequencer. Raw reads will be quality checked using FastQC v0.11.6 (Andrews et al., 2015). QIIME2 will be used to process and analyse the sequence data (Bolyen et al., 2019). Paired end sequences will be denoised by using dada2 (Callahan et al., 2016), and clustered into amplicon sequences variants (ASVs) using ‘vsearch’ with an identity of 0.97 (Rognes et al., 2016). Bacterial ASVs will be annotated using q2‐feature‐classifier plugin (Bokulich et al., 2014). The ASV table will be read into R v3.2.3 for statistical investigation with the vegan package (Dixon, 2003).

Blood and stool samples are stored at BIOBANK General Hospital of Vienna and BIOBANK of the Medical University of Innsbruck. All samples will be labelled with study pseudonyms containing the respective measurement time point and dates of sampling.

